##### GERD recurrence

GIS questionnaire scores will be compared between each arm using a generalized linear mixed model to account for the random effect of GP’s practice.

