**Discussion:**

Based on previous trials, we anticipate more than 10% “successful PPI deprescribing” in the multi-faceted intervention compared to the single intervention on GPs and the control arm*.* The study has been funded through a national grant and will be launched in autumn 2020, for early results by the end of 2022.

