### Trial objectives

The primary objective of this study is to assess if a multi-faceted intervention is superior to single intervention and usual care to increase PPI deprescribing. Three arms will be compared: i) a multi-faceted intervention with patients using a patient education brochure and with their general practitioners (GPs) using both a personalized letter and a deprescribing algorithm ii) a single intervention on GPs and iii) no intervention (usual care).

Secondary objectives are to assess if the multi-faceted intervention has an economic efficiency compared to control group by performing a cost-utility analysis, to determine the gastroesophageal reflux disease (GERD) symptom recurrence rate, the patients’ attitudes toward deprescribing, and the characteristics of patients engaging in the deprescribing process.

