#### Secondary outcomes

Incremental cost-utility ratios: cost by quality-adjusted life-years (QALY) ratios comparing the intervention groups to control group. QALYs will be assessed from patient responses to the EuroQoL EQ-5D-5L questionnaire [25].GERD symptom recurrence using the GERD Impact Scale questionnaire [26].Patient attitude towards deprescribing using the French version of the Revised Patient Attitudes Toward Deprescribing (rPATD) [27], the *Attitude des patients envers la déprescription* (APaD) [28].Patient characteristics that succeed in deprescribing PPIs using data collected from health insurance reimbursement database.

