### Sample size and power

Preliminary analyses showed that around 33,000 patients, 1300 GPs and 684 practices would meet inclusion criteria in 2017, which corresponds to a mean of 1.9 GPs and 48.3 patients per practice. Using an intraclass correlation coefficient (ICC) of 0.05 thus lead to an inflation factor of 3.365. Literature data suggested a “natural” PPI deprescribing rate between 2 and 7% in the control arm [17, 20, 30].

Assuming an inflation factor of 3.365 and using a two- sided alpha of 0.05, we will have 90% power to detect a minimum true difference of 9.5% of PPI deprescribing rates between the multi-faceted intervention arm and the control arm. These estimates change slightly if different natural deprescribing rates and higher ICCs are assumed (Table 1).

**Table 1 Tab1:** Sample size simulation

“Natural” PPI deprescribing rate	PPI deprescribing rate due to intervention	Patients per cluster	Intracluster Correlation Coefficient	Power
2%	17%	45	0.05	> 0.999
2%	17%	50	0.05	> 0.999
2%	17%	45	0.1	> 0.999
2%	17%	50	0.1	> 0.999
2%	10%	45	0.05	> 0.999
2%	10%	50	0.05	> 0.999
2%	10%	45	0.1	> 0.999
2%	10%	50	0.1	> 0.999
7%	17%	45	0.05	> 0.999
7%	17%	50	0.05	> 0.999
7%	17%	45	0.1	> 0.999
7%	17%	50	0.1	> 0.999
7%	10%	45	0.05	> 0.994
7%	10%	50	0.05	> 0.990
7%	10%	45	0.1	> 0.930
7%	10%	50	0.1	> 0.908

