### Plan of statistical analyses

The analyses of primary and secondary outcomes will follow a modified intention-to-treat principle (mITT). All initially randomized patients and GPs and will be included in the analysis according to the group to which they were assigned, minus those who did not fulfil the inclusion criteria after randomization (for example patients with a PPI deprescribing occurring between randomization and intervention).

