#### Limitations

Despite these strengths, our trial has several limitations. Firstly, regarding the deprescribing rate and the cost-utility analysis, our data will be collected from the health insurance reimbursement database. This database only estimates the consumption of medications through their reimbursements [37]. PPI consumption can be overestimated because real patient intake depends on adherence. Conversely, this database does not compile over-the-counter PPI but they are less used than reimbursable PPI [38].

Secondly, the secondary outcome on GERD recurrence is assessed by the GERD impact scale questionnaire at 12 months after baseline. Thus, we may miss GERD recurrence caused by an early acid rebound due to PPI withdrawal. However, sending this questionnaire during the intervention may influence patients’ perceptions, resulting in a participation bias on the primary outcome. We chose to keep our trial without further interventions during the study period. The GERD impact scale will only assess the GERD recurrence following PPI deprescribing.

Thirdly, neither patients nor their GP will be blinded because of the pragmatic trial design [39]. However, the participants will not be informed of the different interventions occurring during the year of the trial. Data managers and statisticians will be blinded to the allocation arm. Primary outcome (PPI deprescribing) is objective and not subject to interpretation.

Fourthly, because of logistical constraints, only a 10% sample of the population (nearly 3300 patients) will have the opportunity to answer questionnaires on secondary outcomes. The questionnaires will be sent by mail and the number of participants will depend on response-rate. However, the response-rate should be increased due to pre-paid return envelopes and amplified by phone reminders, as reported by Neve et al. for patient reported outcomes [40].

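### The GERD objective is a recurrence rate after deprescribing, but the only stated analysis compares scores between whole arms, which gives no rate and would probably miss marked worsening in most of the plan's own scenarios

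*Protocol article*

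**What the plan says.** All references are to the protocol article.

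- **Trial objectives**: one secondary objective is "to determine the gastroesophageal reflux disease (GERD) symptom recurrence rate".
- **Secondary outcomes**: the outcome is "GERD symptom recurrence using the GERD Impact Scale questionnaire".
- **Limitations**: after conceding that early acid rebound may be missed, the text says "The GERD impact scale will only assess the GERD recurrence following PPI deprescribing".
- **Secondary analyses, GERD recurrence**: the whole analysis is that "GIS questionnaire scores will be compared between each arm using a generalized linear mixed model", with a random effect for practice.
- **Plan of statistical analyses**: "The analyses of primary and secondary outcomes will follow a modified intention-to-treat principle (mITT"), so patients are analysed in their assigned arm whether or not they deprescribed.
- **Sample size and power**: the literature is said to suggest a natural "PPI deprescribing rate between 2 and 7% in the control arm". The Table 1 column headed "PPI deprescribing rate due to intervention" takes the values 10% and 17%.
- **Data collection procedures and Timeframe**: the scale is mailed to a 10% sample one month before and 12 months after baseline, and the databases are paired at patient level.

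**The concern.** The objective and the Limitations section describe an event that follows withdrawal and ask how often it happens. The analysis answers another question: whether symptom scores differ between arms. No rate comes out of it, and deprescribing status plays no part. Condensing a protocol into an article does not readily explain this, because the adjacent section on patient attitudes does cross-tabulate responses with successful deprescribing. The link is missing for the outcome whose objective depends on it.

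The GERD Impact Scale is the trial's only reflux-specific symptom outcome, and the Conclusion looks ahead to national use and to other medicines. By the plan's own rates, 83% to 90% of an intervention arm is not expected to reach the 50% reduction, so any worsening among those who do is averaged over the whole arm. A non-significant result reported under the heading of GERD recurrence could be taken as evidence that symptoms do not return after deprescribing, when the comparison often had little chance of showing it.

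**Working it through.** **Reproducing the plan's figures.** 33,000 patients / 684 practices = 48.3 per practice (rounded up), and the inflation factor is 1 + (48.3 − 1) × 0.05 = 3.365, as printed. With 33,000 / 3 = 11,000 patients per arm and two-sided alpha 0.05, power for 7% v 10% is 0.9938, 0.9903, 0.9299 and 0.9076 for the four combinations of cluster size and ICC. This matches the last four rows of Table 1. No power is stated for the GERD outcome.

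**Inputs for the GERD comparison.** From the protocol: a 10% sample of about 3,300, so 1,100 per arm; 684 / 3 = 228 practices per arm; the Table 1 deprescribing rates. Assumed: the ICC of 0.05 carries over to the score; response is 100% or 50% (no rate is stated); only patients reaching the 50% reduction worsen, by d SD on average; no adjustment for the pre-baseline score, since none is stated.

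**Dilution.** Arm difference = d × (intervention rate − control rate). The four scenarios give 0.03d (7% v 10%), 0.08d (2% v 10%), 0.10d (7% v 17%) and 0.15d (2% v 17%).

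**Detectable arm difference at 80% power**, 2.80 × √(2 × DE / n):
- Full response: 1,100 / 228 = 4.82 per practice, DE = 1 + 3.82 × 0.05 = 1.191; 2.80 × √(2 × 1.191 / 1,100) = 0.130 SD.
- 50% response: 550 / 228 = 2.41 per practice, DE = 1.071; 2.80 × √(2 × 1.071 / 550) = 0.175 SD.

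Dividing by the dilution factor gives the worsening needed per extra deprescriber. Power for fixed values of d is alongside.

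| Control v intervention | SD needed, 100% / 50% response | Power, d = 0.8, 100% / 50% | Power, d = 1.0, 100% / 50% |
|---|---|---|---|
| 7% v 10% | 4.4 / 5.8 | 7% / 6% | 9% / 7% |
| 2% v 10% | 1.6 / 2.2 | 28% / 18% | 41% / 25% |
| 7% v 17% | 1.3 / 1.75 | 41% / 25% | 58% / 36% |
| 2% v 17% | 0.87 / 1.17 | 73% / 49% | 90% / 67% |

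**The same check on a rate.** Suppose recurrence is 20% without deprescribing and 50% with it (both assumed). At 7% v 17% the arm rates are 0.93 × 0.20 + 0.07 × 0.50 = 22.1% and 0.83 × 0.20 + 0.17 × 0.50 = 25.1%. Power over the four scenarios, in table order, is 7%, 24%, 33% and 63% at full response, and 5%, 15%, 20% and 40% at 50% response. With a 10% background instead, it is 11%, 55%, 68% and 96%, and 8%, 34%, 44% and 80%. The size of the problem depends heavily on these assumptions.

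**The case against.** The arm comparison is legitimate. The trial tests mailed strategies pragmatically, and the comparison by assigned arm is the randomised estimate of each strategy's effect on symptoms. Comparing deprescribers with others is confounded. This stands, and it is why the comparison should be kept. The fault is only that it stands alone for a different question.

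A reader might infer that any marked recurrence must end in a null result. The plan's figures do not support that: at 2% v 17% with full response, power is 73% for 0.8 SD and 90% for 1.0 SD. Adjusting for the pre-baseline score would also help. With an assumed correlation of 0.5, the required differences shrink by a factor √(1 − 0.25) = 0.87, for example from 1.75 to about 1.5 SD.

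A reader might also infer that patients who miss the criterion cannot have withdrawal symptoms. The criterion is a 50% fall in yearly dispensing, so someone who cut by less, or who stopped, relapsed and restarted, may well have had symptoms. Such patients could add signal between arms, which the dilution model sets to zero.

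For the same reason, a recurrence rate confined to patients who meet the 12-month criterion can understate harm, because those who relapsed and restarted drop out of it. Any remedy has to deal with this.

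Finally, a cut-off for recurrence may be in a full protocol or analysis plan that is not shown, so its absence from the article is not counted as a fault. The protocol nowhere says that a null result will be read as absence of recurrence; that is a risk to guard against. It also openly acknowledges the small sample and the dependence on response.

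**Conclusion.** The point holds in limited form. The objective (a recurrence rate, described as following deprescribing) and the stated analysis (scores between arms under mITT) do not match, and the analysis as written cannot deliver the rate.

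The arm comparison is valid for the strategy's effect but insensitive to worsening among deprescribers. A 0.8 SD worsening is more likely missed than found in three of the four Table 1 scenarios at full response, and in all four at 50% response. A 1.0 SD worsening is more likely missed in two of four and three of four respectively. These figures rest on the assumed score ICC, the assumed response, no baseline adjustment, and no worsening below the 50% threshold. A higher response, baseline adjustment or symptoms after smaller reductions would all improve the picture. The mismatch itself rests on none of these assumptions.

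**What to change.** 1. Keep the comparison by arm and adjust it for the pre-baseline GERD Impact Scale score, which is already collected.
2. Define recurrence as a worsening from the patient's own pre-baseline score, with the size of change fixed in advance, and report its rate by arm with confidence intervals that allow for practice.
3. As a supportive, non-randomised analysis, report that rate by degree of PPI reduction. Show separately patients who met the 50% criterion and those who reduced and then resumed dispensing, so that relapsers who restarted are not lost.
4. An estimate using arm as an instrument is optional. It must state its assumption that the mailing affects symptoms only through reaching the 50% threshold, which smaller reductions would break.
5. State that a null arm comparison alone does not support a claim of no recurrence after deprescribing.

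The cost is analysis wording and a few added estimates, with no new questionnaires. Item 3 needs dispensing dates from the reimbursement database; the article describes yearly totals, so their availability should be confirmed.

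The supportive contrast is confounded and must be labelled so. Precision will be modest: if 10% of the sample deprescribes (assumed), that is 330 patients at full response and 165 at 50%. Ignoring clustering, the 95% interval for a rate near 50% is then about ±1.96 × √(0.25 / 330) = ±5.4 points or ±1.96 × √(0.25 / 165) = ±7.6 points. The instrument estimate would be much less precise.

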##### Patient attitudes toward deprescribing

Cross-tabulations between the different rPATD questions and patient characteristics, and successful deprescribing at 12 months will be performed using Cochran-Armitage tests. Patient attitude measured from Likert scale will be compared between each arm with a generalized linear mixed model to account for the random effect of GP’s practice.

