## Methods

### Study design and setting

The trial is designed as a prospective, open-label, cluster-randomized parallel-controlled study within a 12-month period. The unit of randomization will be the GPs practice. This pragmatic population-based trial will be conducted in every eligible GP practice in two regions of Western France (Loire-Atlantique and Vendée).

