### Recruitment and allocation

Each GP practice and its associated patients will be defined as an individual cluster to avoid contamination bias between GPs and/or between patients [21]. These clusters will be randomized in three arms using a 1:1:1 ratio. Eligible patients will be identified using the local health insurance reimbursement database.

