##### Characteristics of patients succeeding in PPI deprescribing

Association of patient characteristics (age, sex, socio-economic status, chronic disease, GP) and PPI deprescribing success will be tested with a generalized linear mixed model to account for the random effect of GP’s practice.

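### The tests linking rPATD answers to deprescribing success treat patients as independent and, as stated, ignore arm; a mixed model on pre-mailing answers would remove both problems

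*Protocol article*

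**What the plan says.** The section on patient attitudes toward deprescribing names one method for two sets of associations, rPATD items with patient characteristics and rPATD items with success: "Cross-tabulations between the different rPATD questions and patient characteristics, and successful deprescribing at 12 months will be performed using Cochran-Armitage tests". It mentions no practice effect and no stratification by arm. The next sentence takes another route for the arm comparison: "Patient attitude measured from Likert scale will be compared between each arm with a generalized linear mixed model", and gives the random effect of practice as the reason. The primary analysis, the GERD analysis and the analysis of characteristics of successful patients also use a mixed model with a practice effect.

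On design, "The unit of randomization will be the GPs practice" and "These clusters will be randomized in three arms using a 1:1:1 ratio". Under data collection procedures, the rPATD goes to a 10% patient sample in each arm, once a month before baseline and once 12 months after. The attitudes section does not say which of the two sets of answers is related to success.

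**The concern.** There are two separate issues.

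**Clustering.** A Cochran-Armitage trend test takes its variance from independent patients. Patients of one practice share prescribers, so success is correlated within practice, and the protocol allows for this almost everywhere else. If the attitude item or patient characteristic is correlated within practice too, the test is too liberal.

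**Arm.** The brochure is meant to raise success and may well change attitudes. If 12-month answers are used with the three arms together, the multi-faceted arm can have both more favourable attitudes and more successes. The test would then show an association even if attitude and success were unrelated among patients of the same arm. A reader would take that as evidence that attitude predicts deprescribing, when it only reflects who received the brochure.

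**Working it through.** **Inputs from the protocol article.** Sample size and power: "around 33,000 patients, 1300 GPs and 684 practices would meet inclusion criteria in 2017"; 48.3 patients per practice; ICC 0.05, with 0.1 also used in Table 1; natural rate 2% to 7%; intervention rate 10% or 17%. Limitations: nearly 3300 patients in the 10% sample.

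**Assumptions.** The sample is spread evenly over practices (48.3 × 0.10 = 4.83 per practice). The ICC of a patient-level item is 0.05 or 0.1. There are 1,650 responders (half of 3300). The brochure shifts the 12-month attitude by 0.2 to 0.5 SD in the multi-faceted arm only. The success rate in the single-intervention arm is 10%, or 7% in the low case.

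**The plan's own figure.** Inflation factor = 1 + (m − 1) × ICC = 1 + 47.3 × 0.05 = 3.365, as stated.

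**Step 1: clustering alone.** For a trend test of success y on covariate x, the design effect is DE = 1 + (m − 1) × ICC_y × ICC_x. The true two-sided error is 2 × [1 − Φ(1.96/√DE)].

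| m | ICC_y | ICC_x | DE | True error |
|---|---|---|---|---|
| 4.83 | 0.05 | 0.05 | 1.0096 | 5.1% |
| 4.83 | 0.1 | 0.1 | 1.0383 | 5.4% |
| 4.83 | 0.05 | 1 (constant in practice) | 1.1915 | 7.3% |
| 4.83 | 0.1 | 1 (constant in practice) | 1.383 | 9.6% |
| 48.3 (whole practices sampled) | 0.05 | 0.05 | 1.118 | 6.4% |
| 48.3 (whole practices sampled) | 0.1 | 0.1 | 1.473 | 10.6% |

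Non-response lowers m and so the error. At 50% response (m = 2.42), patient-level items with both ICCs equal are at 5.04% to 5.16%.

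**Step 2: arm, if 12-month answers are used.** Take equal arms, mean attitudes (0, 0, s) in SD units, success rates (p0, p1, p2), and no association within any arm. The pooled correlation is r = cov/√(V_x × V_y), where cov is the between-arm covariance, V_x = 1 + 2s²/9 and V_y = p̄(1 − p̄). The rejection rate follows from the noncentrality r × √1650.

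- Rates 7/10/17%: p̄ = 0.1133, V_y = 0.1005.
  - s = 0.2: cov = 0.00378, r = 0.012, noncentrality 0.48, rejection 7.7%.
  - s = 0.5: cov = 0.00944, r = 0.029, noncentrality 1.18, rejection 21.8%.
- Rates 7/7/10%: p̄ = 0.08, V_y = 0.0736.
  - s = 0.2: noncentrality 0.20, rejection 5.5%.
  - s = 0.5: noncentrality 0.49, rejection 7.7%.

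**Step 3: simulation.** This used 684 practices, about 4.83 respondents each (full response), a five-level item, half of the shift in the single-intervention arm, and 4000 runs per setting.

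- No attitude shift, patient-level item: the pooled test rejects in 4.8% to 5.7% of runs.
- Shift of 0.2 to 0.4 SD: the pooled test rejects in 6% (rates 7/8.5/10%) to 46% (rates 2/9.5/17%, shift 0.4). The same test stratified by arm rejects in 5% to 6%.

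Accounting for arm therefore removes the distortion. With answers given before the mailing it should not arise in the first place.

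**The case against.** The strongest reply is that this is an exploratory secondary analysis in a 10% sample and that the text does not commit to the harmful version. In the quoted sentence, the 12-month time point belongs to success and not to the rPATD answers. If the pre-mailing answers are used, arm cannot have changed them and the error stays near 5%. The test can also be run within arms or stratified by arm. The shift in attitude and the number of responders are not in the documents. All of this stands, and it limits the size of the point. It does not remove it: the section fixes a test, states no stratification, leaves the questionnaire wave open and departs from the mixed-model approach used in its own next sentence.

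A reader might go further and infer that the analysis of who succeeds is also faulty, because "Association of patient characteristics (age, sex, socio-economic status, chronic disease, GP) and PPI deprescribing success will be tested with a generalized linear mixed model" and the bracketed list contains neither arm nor baseline PPI amount. The documents do not support that. The list names the characteristics under study in a condensed article and is not a full model specification. That model already has a practice effect. Randomization balances baseline characteristics across arms, so leaving arm out would not confound their association with success. The objective, "the characteristics of patients engaging in the deprescribing process", is descriptive and does not ask for whom the brochure works, so arm-by-characteristic terms would answer a different question.

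**Conclusion.** The point holds for the Cochran-Armitage tests only. They are a weaker choice than the mixed model used beside them, for a reason that the protocol itself accepts.

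It would be too strong to say that the p-values are wrong throughout. For patient-level items in an evenly spread sample, the loss from clustering is a few tenths of a percentage point. It becomes noticeable only for covariates constant within practice, or if whole practices were sampled, and the sampling method is not given. The material distortion, about 8% to 22% in the main scenario and about 5% to 8% in the low one, depends on 12-month answers being used and on the assumed brochure effect, response and single-arm rate.

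The primary analysis, the between-arm comparisons and the model for characteristics of successful patients are untouched.

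**What to change.** In the section on patient attitudes, replace the Cochran-Armitage tests of success with a logistic mixed model. Its outcome is success at 12 months. The rPATD item from the pre-mailing questionnaire enters as a linear score, arm as a fixed effect and practice as a random effect. The linear score keeps the trend character of the test now named. For rPATD items against patient characteristics, use a corresponding mixed model with practice as random effect. State in the text that the pre-mailing answers are the ones related to success.

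The cost is a change of wording and a little more analysis work. Item answers, arm, practice and success are already part of the planned data, so nothing further has to be collected.
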